## Abstract

**Background:**

Vaccination with dendritic cells (DC) loaded with tumor antigens elicits tumor-specific immune responses capable of killing cancer cells without inducing meaningful side-effects. Patients with advanced melanoma enrolled onto our phase II clinical studies have been treated with autologous DC loaded with autologous tumor lysate/homogenate matured with a cytokine cocktail, showing a clinical benefit (PR + SD) in 55.5% of evaluable cases to date. The beneficial effects of the vaccine were mainly restricted to patients who developed vaccine-specific immune response after treatment. However, immunological responses were only induced in about two-thirds of patients, and treatments aimed at improving immunological responsiveness to the vaccine are needed.

**Methods/Design:**

This is a phase II, “proof-of-principle”, randomized, open-label trial of vaccination with autologous DC loaded with tumor lysate or homogenate in metastatic melanoma patients combined with immunomodulating RT and/or preleukapheresis IFN-α. All patients will receive four bi-weekly doses of the vaccine during the induction phase and monthly doses thereafter for up to a maximum of 14 vaccinations or until confirmed progression. Patients will be randomized to receive:

(1.) three daily doses of 8 Gy up to 12 Gy radiotherapy delivered to one non-index metastatic field between vaccine doses 1 and 2 and, optionally, between doses 7 and 8, using IMRT-IMAT techniques;

(2.) daily 3 MU subcutaneous IFN-α for 7 days before leukapheresis;

(3.) both 1 and 2;

(4.) neither 1 nor 2.

At least six patients eligible for treatment will be enrolled per arm. Daily 3 MU IL-2 will be administered subcutaneously for 5 days starting from the second day after each vaccine dose. Serial DTH testing and blood sampling to evaluate treatment-induced immune response will be performed. Objective response will be evaluated according to immune-related response criteria (irRC).

**Discussion:**

Based upon the emerging role of radiotherapy as an immunologic modifier, we designed a randomized phase II trial adding radiotherapy and/or preleukapheresis IFN-α to our DC vaccine in metastatic melanoma patients. Our aim was to find the best combination of complementary interventions to enhance anti-tumor response induced by DC vaccination, which could ultimately lead to better survival and milder toxicity.

## Background and rationale

### Malignant melanoma

Malignant melanoma represents one of the most challenging problems in modern oncology. Although it accounts for only 4% of incident cases of skin cancers, it is responsible for more than 80% of all skin cancer deaths [1]. Moreover, its incidence has dramatically increased in recent decades [2]. Whilst early stage melanoma (i.e. primary thin melanomas without regional lymph node or distance involvement) has a very favourable prognosis with a recurrence rate of less than 10% at five years, patients with advanced disease experience a very poor clinical course, with median survival ranging from 4 to 12 months [3]. Furthermore, until very recently, the clinical efficacy of the available treatments was disappointing. In early 2011, the FDA approved the clinical use of ipilimumab, a CTLA 4-blocking monoclonal antibody which, in addition to significantly improving the survival of patients with metastatic melanoma, primarily demonstrated the effectiveness of anti-cancer therapy based only upon immune system targeting [4,5]. However, ipilimumab causes a generalized activation of the immune system which can, in extreme cases, induce severe autoimmune side-effects [6]. On this basis, immunotherapeutic approaches capable of eliciting effective anti-tumor immune responses without the related autoimmunity must be sought developed.

### Dendritic cell vaccination

Vaccination with dendritic cells (DC) loaded with tumor antigens has been shown to elicit tumor-specific immune responses potentially capable of killing cancer cells without inducing significant side-effects [7]. DC are widely distributed antigen-presenting cells that play a central role in the activation and regulation of the immune response [8]. In particular, DC determine the final outcome of adaptive immune responses against a specific antigen, *i.e*. whether it will be tolerated or whether a specific immune response will be triggered against it. The final outcome depends on the balance between different signals acting on the DC and DC antigen uptake. Indeed, if immature DC recruited to peripheral tissues find appropriate “danger signals” (*i.e*. pathogen products capable of triggering toll-like receptors), they undergo maturation and migrate to lymph nodes where they initiate a specific immune response. Conversely, if danger signals are not present, or if concurrent immunosuppressive stimuli occur, DC maturation does not take place, thus inducing immune tolerance against the antigens they are presenting [8]. As cancer progresses, tumor cells acquire the ability to evade the immune response by selecting lesser immunogenic variants (“cancer immunoediting”) [9,10] and/or by producing immunosuppressive cytokines and other biologically active substances that strongly influence the ability of DC to prime and sustain effective immune responses [11,12].

In 1996, Schadendorf’s group was the first to test, in melanoma patients, the feasibility of a vaccination strategy aimed at reconditioning DC function by their differentiation and loading with tumor antigens *ex vivo*, thus permitting the effects of a DC-tolerant tumor microenvironment to be overcome [13]. Since this first experience, it has been estimated that over 1,000 patients with different tumors have been treated using different starting cells and differentiation/maturation protocols, as well as different antigen sources and administration routes [14].

Since 2001, patients with advanced melanoma enrolled onto our phase II clinical studies have been administered autologous DC loaded with autologous tumor lysate/homogenate matured with a cytokine cocktail, showing a clinical benefit (PR + SD) in 55.5% of evaluable cases [15,16].

Like de Vries et al. [17], we saw that patients who developed anti-tumor immunity after vaccination experienced a better clinical outcome [16,18]. In particular, we observed that patients developing delayed type hypersensitivity (DTH) against autologous tumor lysate or keyhole lympet hemocyanin (KLH) after at least four courses of the vaccine showed a median overall survival (OS) of 22.9 months compared to the 4.8 months of DTH-negative cases (Log-rank test, p = 0.007) [16]. Intriguingly, both the disease control rate (DCR) and OS obtained with DC vaccination considerably exceeded those obtained with ipilimumab in a similar patient setting [4]. However, although differentiation and maturation conditions used for the production of DC vaccines have been standardized, only two-thirds of patients develop potentially effective anti-tumor immune responses. We recently reported that patients showing upregulated expression of tumor endothelial marker-8 (TEM-8) in monocyte-derived DC upon maturation do not develop immune reactivity against autologous tumor lysate (ATL) or KLH on DTH and experience a very poor clinical outcome after DC vaccination [19].

TEM-8 is an integrin-like cell surface protein specifically expressed by embryonic and tumor endothelial cells (not, however, in the adult endothelium) whose functions are still not fully understood [20]. It was recently shown that TEM-8 is upregulated in tumor-associated endothelial cells after exposure to interleukin-1β (IL-1β) [21]; interestingly, IL-1β, together with tumor necrosis factor-α (TNF-α) and other cytokines produced by tumor cells (melanoma included) [22], can negatively affect the differentiation of monocyte-derived DC in vitro [23]. As IL-1β and TNF-α are components of the cytokine maturation cocktail currently used to prepare the DC vaccine, it would not be surprising that, at least in a subset of patients, these cytokines support the differentiation of DC toward an immunosuppressive TEM-8 + phenotype rather than the more immunogenic and clinically active phenotype. In light of this, new treatment conditions capable of preventing such an occurrence should be identified.

### Potential effects of Interferon-α (IFN-α) on circulating precursors of DC

IFN-α is a cytokine belonging to type-I interferons that is currently approved for clinical use in B-cell non-Hodgkin’s lymphoma, advanced renal cell cancer and, in the adjuvant setting, malignant melanoma. This cytokine is secreted by virtually all cells after challenge with viral or bacterial products, but it can also be produced by transformed cells or by normal cells under mitogenic stimulus. Its effects on tumor or virus-infected cells are pleiotropic, ranging from the direct inhibition of proliferation to the suppression of oncogene expression and the induction of tumor suppressor genes. Moreover, IFN-α positively affects the activity of both the adaptive and innate immune system, and enhances immune recognition of tumor cells [24]. Furthermore, IFN-α inhibits the expression of the proangiogenic inflammatory cytokine, interleukin-8 (IL-8), and IL-1β [25], both of which induce an immunosuppressive phenotype in monocyte-derived DC [23].

It is tempting to speculate that treatment with IFN-α, whilst inhibiting the expression of IL-1β, may also suppress the maturation-induced TEM-8 upregulation of DC observed in non-immunoresponsive patients, thus revertingthe TEM-8 associated immunosuppressive phenotype. In partial support of this hypothesis is our observation of positive immunization to DTH in all patients who underwent therapy with IFN-α a maximum of 30 days before starting DC vaccination (our unpublished data), suggesting that IFN-α priming performed *in vivo* before leukapheresis may enhance the immunostimulatory profile of DC. Moreover, IFN-α priming may also have a “mobilizing” activity on DC precursors: it was recently reported that 1–3 MU subcutaneous IFN-α enhances the proportion of circulating CD14+ and CD14 + CD16+ monocytes in both healthy donors and melanoma patients [26].

In the light of these findings, administration of IFN-α before leukapheresis may positively modulate the immunological and clinical efficacy of DC vaccination.

In particular, preemptive IFN-α should:

– (1.) lead to the production of more highly immunogenic monocyte-derived DC;

– (2.) mobilize peripheral DC precursors, thus enhancing leukapheresis yields;

– (3.) positively modulate the immunogenicity of melanoma cells *in vivo*.

### Immunomodulating effects of radiotherapy

Ionizing radiation therapy (RT) is known for its capacity to kill cancer cells and other cells within the tumor stroma, including endothelial cells and intratumoral lymphocytes [27]. Although tumor cells killed by RT may represent a suitable source of antigens for DC uptake and presentation to T cells, it is widely accepted that optimal activation of T cells by DC can be achieved only in the presence of inflammatory or “danger” signals. On this basis, the hypothesis that exposure to ionising radiation (IR) generates a proinflammatory “danger” microenvironment supports claims made of a strong synergy between radiotherapy and immunotherapy. In particular, IR induces the secretion of the pro-inflammatory cytokines IL-1β and TNF-α in both animal cancer models and cancer patients [28,29]. Moreover, IR upregulates the expression of Fas/CD95 receptor and NKG2D-L in cancer cells [30], encouraging the recognition and killing of the “altered self” and MHC-I and co-stimulatory molecules, which leads to a more accurate recognition by immune effectors [31]. Finally, RT can facilitate the homing of both antigen-presenting and effector T cells to the tumor bed by eliciting inflammatory signals and changes in extracellular matrix proteins and by inducing the expression of adhesion molecules by endothelial cells in the tumor microenvironment [32,33]. Demaria S. *et al*. showed that irradiation of a tumor xenograft in a murine model protected against rechallenge from the same tumor cells outside the irradiation field. This anti-tumor effect was probably the result of a specific immune response as it is not observed in immunodeficient nude mice. It would seem to be tumor-type specific *i.e*. (growth of a second graft of a different cell line is not affected by irradiation of the first graft) and is synergistic with administration of the Flt-3 (FMS-like tyrosine kinase 3) ligand. Flt-3 alone (no RT) has no effect on the second graft, probably because of a nonspecific immunity boost provided by the Flt-3 ligand. Overall, these data suggest that RT delivered to a tumor site may also prime the immune system against related tumor cells at some distance from the irradiation field (“abscopal effect”) and that, in the absence of additional immune system stimulation, the radiation-induced immune response has no clinical effect. Accordingly, the combined use of DC vaccination and RT with “immunological” intent should theoretically strengthen the effect of the vaccine by acting as an *in situ* boost in which tumor antigens are released and captured by intratumoral DC in a microenvironment positively conditioned by ionising radiation [34-37].

### Description of the investigational product

Since 2001, IRST Somatic Cell Therapy Laboratory has produced an advanced medicinal product in the form of a therapeutic vaccine composed of autologous DC pulsed with autologous tumor lysate or homogenate for patients with metastatic melanoma or kidney cancer [15,16,38-40]. The vaccine can be administered to patients either immediately after preparation or after thawing of cryopreserved aliquots. Details on manufacturing methods are provided in Additional file 1.

### Freshly-prepared vaccine

Each vaccine dose is prepared from patients’ monocytes obtained by leukapheresis. After leukapheresis, a part of the monocytes obtained are cultured and the remainder is cryopreserved in aliquots to be used for the manufacture of subsequent vaccine doses. Monocytes are cultured for six days in serum-free, GMP (Good Manufacturing Practice) certified medium supplemented with granulocyte-macrophage colony-stimulating factor (GM-CSF) and interleukin-4 (IL-4) to obtain immature dendritic cells (iDC). These immature DC are pulsed with autologous lysate or homogenate prepared from surgically removed metastatic lesions. After pulsing, DC are then matured for 48 hours in the presence of a cytokine cocktail (TNF-α, IL-1β, IL6, and PGE2). Mature DC (mDC) are then collected, washed, counted and re-suspended in sterile saline (total 7–15 × 10^6^ cells) for immediate intradermal administration to patients.

### Cryopreserved vaccine

The vaccine is produced from the whole leukapheresis product according to the previously described protocol. After the maturation step, pulsed mDC are collected, washed, counted, re-suspended in sterile saline, aliquoted (total 7–15 ×10^6^ cells) and cryopreserved by automated freezing. Before administration, the mDC are thawed, washed, re-suspended in saline and immediately injected intradermally into patients.

### Delayed-type hypersensitivity test (DTH)

DTH testing is a classic method for measuring cellular immune reactivity. This technique involves the intradermal administration of an antigen preparation and the monitoring of the degree of erythema and induration produced 24–48 hours after injection. The response reflects antigen-specific recruitment and the activation of CD4+ to release T-helper 1 cytokines (in particular, IFN-α) and CD8+ effector T cells into the injection site [41,42]. In our experience, as in that of other groups, a positive response to the DTH test performed with soluble antigen (in our studies with ATL) after vaccination with DC in metastatic melanoma patients was strongly correlated with a better clinical outcome [15-18]. DTH testing using another antigen, KLH, has been studied and its positivity has also been found to be associated with improved clinical outcome in vaccinated patients. We use KLH as an immunological adjuvant in the preparation of our DC vaccine and have seen that positive DHT testing to this protein is a reliable indicator of immunologic competence in vaccinated patients. DTH testing does not require extensive training or the use of costly equipment and can easily be performed at the patient’s bedside. All these features make it a feasible, low-cost immunomonitoring method that permits the evaluation of immunologic efficacy in a clinical trial setting.

### Trial design and statistical considerations

This is a phase II, randomized, open-label trial aimed at assessing whether different external immunostimulant conditions, *i.e*. preleukapheresis IFN-α and external RT to one target lesion, enhance, alone or in combination, the immunological efficacy of autologous DC loaded with tumor lysate or homogenate in metastatic melanoma patients. The design follows the concept of “proof-of-principle” studies [43,44] in which the rationale for a given treatment or treatment combination is explored by analyzing disease and/or treatment-specific biological parameters. The study has been approved by the Local Ethics Committee (ClinicalTrails.gov identifier: NCT01973322) and will be carried out in compliance with the Helsinki declaration.

Therapeutic cancer vaccines are a heterogeneous group of complex biologics with distinctly different clinical characteristics which require the development of new clinical paradigms. Hoos *et al*. proposed the use of a “proof-of-principle” trial which would include patients in a metastatic setting without rapidly progressive disease to allow vaccines to have sufficient time to induce biological activity and which would also incorporate immune and molecular markers.

Our objectives include the demonstration of biological activity as proof-of-principle, defined as any effect of the vaccine combination on the target disease using biological markers as study endpoints (immunological response). We also aim to identify which, if any, external immunostimulant conditions give the best result in terms of biological activity, *i.e*. improving the ability of the DC vaccination to induce clinically effective anti-tumor immune responses. We chose the randomized design to select the most promising regimen for further evaluations (phase II or phase III trials) [45,46]. This approach, based upon the assumption that immunotherapy is only expected to be effective in patients showing efficient induction of anti-tumor immune responses (“targeted endpoint”), allows us to reduce the number of patients required to evaluate the potential efficacy of an experimental treatment.

Randomization guarantees the avoidance of selection bias, excluding the preferential inclusion of patients in certain treatment arms. This approach, whilst not identifying which factors contribute to immunogenicity or which regimens are significantly better than others, will, however, highlight a treatment or treatment combination that warrants further investigation. The sample size per treatment must be large enough to ensure, with strong probability, that if one treatment or treatment combination is superior to all others by a specific amount, then it will have the largest sample mean and will therefore be selected. In particular, if one of the external immunostimulant conditions investigated shows higher clinical activity than that observed in the other conditions by a predetermined amount, that condition will be superior to the others with a given probability and will merit further clinical investigation. By enrolling six patients in each treatment arm, we will obtain a 90% probability of correctly selecting the best investigated external immunostimulant condition if the superior arm, if present, has a true expected outcome that is at least 15% higher in terms of irDCR (immune-related disease control rate) than that of the inferior arms [46]. Otherwise, the immunological primary endpoint (immunological efficacy) will guide the choice of treatment combination to further develop using the same method. If a treatment or a combination of treatments is not identified as superior, the vaccine regimen (without external immunostimulant conditions) will be considered for further investigation.

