#### Leukapheresis and vaccine manufacturing

At the end of the screening phase, patients will be randomized and will enter the leukapheresis and vaccine manufacturing phase. Each patient will be assigned to one of the following arms:

(1.) three daily doses of 8 Gy - 12 Gy radiotherapy delivered to one non-index metastatic field (optional to one additional field) between vaccine doses 1 and 2 and between doses 7 and 8, using IMRT-IMAT techniques;

(2.) daily 3 MU subcutaneous IFN-α for 7 days before leukapheresis;

(3.) both 1 and 2 external immunostimulant conditions;

(4.) neither 1 nor 2 external immunostimulant conditions.

At least six patients eligible for treatment will be enrolled per arm.

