### Sample size

This is a “randomized selection design” study based on the assumption that immunotherapy is expected to be effective only in patients showing efficient induction of antitumor immune responses (“targeted endpoint”) [49]. The Steinberg and Venzon approach permits the researcher to select one among a number of different treatment arms as being worthy of further evaluation in a subsequent study. This method requires an adequate gap in the number of immune responses among different arms be observed in order to limit the probability that the selected arm is, in actual fact, inferior to the others. Assuming an error probability of selecting an inferior arm of 10%, a gap of 2 patients with an immune response out of a total of 6 enrolled patients per arm is sufficient, regardless of the proportion of irOR expected in each arm, to show that the difference between the highest probability of response and the best response of the remaining arms is 15%. If the gap is inferior to 2 patients, no treatment arm can be considered better than another and new immunostimulating therapies will have to be identified to combine with the DC vaccine.

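### Six patients per arm do not give a 90% probability of selecting an arm that is truly 15 points better: by highest count it is about 46–49%, and about 9–16% if the two-patient gap rule is applied

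*Protocol article*

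**What the plan says.** The article treats selection in two places.

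- **Trial design and statistical considerations:** with six per arm, "we will obtain a 90% probability of correctly selecting the best investigated external immunostimulant condition", on condition that the superior arm "has a true expected outcome that is at least 15% higher in terms of irDCR". The rule described is that if one arm is truly better by the set amount, "then it will have the largest sample mean and will therefore be selected". The immunological endpoint is to guide the choice otherwise, by the same method. If no arm is identified as superior, vaccine alone is considered for further study.
- **Sample size:** the allowance for a wrong choice is set first: "Assuming an error probability of selecting an inferior arm of 10"%. The lead then required is given as follows: "a gap of 2 patients with an immune response out of a total of 6 enrolled patients per arm is sufficient". This is said to hold whatever the response proportion, and to show a 15% difference between the best arm and the next best. For smaller leads the rule is: "If the gap is inferior to 2 patients, no treatment arm can be considered better than another". In that case other stimulating treatments are to be sought.

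Leukapheresis and vaccine manufacturing lists four arms: radiotherapy, IFN-α, both, neither. Neither section assumes a base rate.

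**The concern.** A 10% limit on choosing an inferior arm and a 90% probability of choosing the best arm are complements only if an arm is always chosen. Under the gap rule, no choice is a third outcome, and with six patients per arm it could be the most common one. Under the highest-count rule an arm can always be named once ties are broken, but six binary outcomes per arm carry little information about a 15-point difference.

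The figure matters because the article attaches decisions to a null result: vaccine alone goes forward, or different stimulants are sought. A reader who believes the 90% would take no selection as good evidence that neither radiotherapy nor IFN-α helps.

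**Working it through.** **Inputs.** n = 6 per arm; k = 4 arms (k = 3 if only the three stimulant arms compete); advantage 0.15, read as percentage points. No base rate p is given, so p was scanned from 0 to 0.85. Two reference values come from the Background: clinical benefit in 55.5% of evaluable patients, and immune response in about two-thirds.

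**Model.** Best arm B ~ Bin(6, p + 0.15), with probabilities b(x) and distribution function G. Each other arm ~ Bin(6, p), with probabilities f(x) and distribution function F. All arms independent.

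- Highest count, ties broken at random: Σₓ b(x) Σⱼ C(k−1, j) f(x)ʲ F(x−1)^(k−1−j) / (j+1)
- Gap of at least 2, correct: Σₓ b(x) F(x−2)^(k−1)
- Gap of at least 2, wrong: (k−1) Σₓ f(x) F(x−2)^(k−2) G(x−2)
- No selection: 1 − correct − wrong

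**The article's own figures first.** The 10% limit on selecting an inferior arm reproduces. At a 15-point difference the wrong-selection probability peaks at 8.6% with four arms, 8.8% with three and 8.1% with two. The 90% does not reproduce.

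**Gap rule by hand, four arms, p = 0.555 (best arm 0.705).**

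- x = 4: 0.3225 × 0.2471³ = 0.0049
- x = 5: 0.3083 × 0.5484³ = 0.0508
- x = 6: 0.1228 × 0.8302³ = 0.0703
- x ≤ 3: about 0.0001

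The sum is 12.6% correct. Wrong selection is 6.9%, which leaves 100 − 12.6 − 6.9 = 80.5% with no selection. The complement of the wrong-selection probability is 93.1%, of which 80.5 points are no selection.

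**Results with a true 15-point advantage.**

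| Arms | Base rate | Highest count correct | Gap rule correct | Gap rule wrong | No selection |
|---|---|---|---|---|---|
| 4 | 30% | 47.5% | 15.7% | 8.2% | 76.2% |
| 4 | 40% | 46.5% | 14.8% | 8.6% | 76.6% |
| 4 | 55.5% | 46.7% | 12.6% | 6.9% | 80.5% |
| 4 | 66.7% | 48.5% | 9.4% | 4.0% | 86.6% |
| 4 | 75% | 51.1% | 5.6% | 1.4% | 93.1% |
| 3 | 55.5% | 55.6% | 19.8% | 7.5% | 72.7% |
| 3 | 66.7% | 57.5% | 16.8% | 4.9% | 78.3% |

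Over base rates 0–85% with four arms, the highest count is correct in 46–72% of trials and the gap rule in 1–22%. Over base rates 30–67% with three arms, the figures are 55–58% and 17–22%, with no selection in about 69–78%.

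**Other readings tried.**

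- Reading 15% as a relative increase gives 31–50% by highest count.
- Conditioning on an arm being selected gives 12.6 / (12.6 + 6.9) = 64.6% at p = 0.555.
- Counting every tie as correct gives 61–69% for base rates 20–70%. It reaches 90% only near base rates of 0% or 85%.
- Two arms give at most 81% by highest count.

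For scale, 90% by highest count at p = 0.555 needs about 62 patients per arm (37–67 over the base rates of 10–75% tried).

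**Does a gap of 2 show a 15% difference?** With four identical arms, some arm leads by two or more in 19.1% of trials at p = 0.3, 19.9% at 0.4, 17.7% at 0.555 and 13.1% at 0.667.

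**The case against.** The best defence is that the Sample size section rests six per arm on a different quantity, the limit on choosing an inferior arm, and that limit is correct at the stated 15-point difference. This stands. A reader might infer that the whole basis for the sample size collapses; the document does not support that. Only the 90% statement and the claim about what a gap shows are wrong.

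Second, the two sections use different rules and endpoints: largest mean on irDCR in one, a two-patient gap on immune responses in the other. A reader might take 9–16% as the direct refutation of the irDCR statement. It is not, because nothing says that the gap rule governs irDCR. The direct comparison is 46–49%.

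Third, vaccine alone is treated as the fallback, so three competing arms is an arguable reading. It raises the figures, but nowhere near 90%.

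Fourth, the article admits that it will not identify significantly better regimens and that false positives are likely. This softens the claim about showing a difference, but does not correct a quantified probability.

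A reader might also suppose that six per arm reach 90% for some larger fixed advantage. That is not general: at a two-thirds base rate with four arms, even a best arm at 100% is selected by highest count in only 87.6% of trials.

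**Conclusion.** The 90% probability of correct selection is wrong as written. With four arms of six and a true 15-point advantage, the highest count is correct in about half of trials or fewer at base rates of 30–67%. If the gap rule is applied, correct selection falls to roughly one trial in six to one in eleven, and most trials select nothing. These ranges assume independent binary outcomes and those base rates, which include both of the article's historical rates. Outside them the figures move (the gap rule gives 5.6% at 75%), but by highest count or by the gap rule no base rate from 0 to 85% reaches 90%, with four arms or three.

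That the 90% was obtained by subtracting the 10% error limit from one is a likely explanation, not an established one: the two sections cite different sources, and neither was available. A two-patient gap limits wrong selection at the assumed difference; it does not demonstrate that difference.

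**What to change.** Keep six patients per arm and the 10% limit on selecting an inferior arm. Then:

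1. Delete the 90% statement, and the statement that a gap of two shows a 15% difference.
2. State one selection rule per endpoint, reconciling the largest-mean rule on irDCR with the two-patient gap on immune responses. Say whether vaccine alone competes, and reconcile the two differing consequences of no selection.
3. Give the probabilities of correct, wrong and no selection under that rule, with the base rate and number of arms stated. For example, four arms under the gap rule with a 15-point advantage: 12.6%, 6.9% and 80.5% at a base rate of 55.5% (irDCR); 9.4%, 4.0% and 86.6% at two-thirds (immune response). If the highest count is kept instead: 46.7% and 48.5% correct.
4. State that failure to select an arm is not evidence that the stimulants have no benefit.

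The cost is wording and a much less favourable stated figure. No patients are added.

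### The stated 90% probability of selecting the best arm does not follow from six patients per arm: under the two selection rules given it is 46–72% or 1–22%

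*Protocol article*

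**What the plan says.** Two sections of the protocol article describe how the design behaves with the same six patients per arm and the same 15%.

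- **Trial design and statistical considerations.** A superior arm is expected to show itself because "then it will have the largest sample mean and will therefore be selected". Six per arm is then said to mean that "we will obtain a 90% probability of correctly selecting the best investigated external immunostimulant condition", if the superior arm "has a true expected outcome that is at least 15% higher in terms of irDCR". If irDCR does not settle the choice, the immunological endpoint guides it by the same method. If nothing stands out, the vaccine alone goes forward.
- **Sample size.** The starting point is "Assuming an error probability of selecting an inferior arm of 10"%. A lead of 2 patients with an immune response out of 6 is required, and "If the gap is inferior to 2 patients, no treatment arm can be considered better than another".

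There are four arms, the last being "4.) neither 1 nor 2 external immunostimulant conditions", and "At least six patients eligible for treatment will be enrolled per arm".

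**The concern.** A 10% chance of selecting an inferior arm and a 90% chance of selecting the best arm are complements only if some arm is always selected. The gap rule has a third outcome, no selection, so 1 minus the chance of a wrong selection is the chance of a correct selection plus the chance of none. The trial design section appears to have restated the one as the other.

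The figure supports the primary clinical objective, which is to select the regimen with the best irDCR. A reader who accepts 90% would take a trial in which no arm led as strong evidence that none of the added treatments is 15 points better. The consequence is real: after such a result the trial design section turns to the vaccine alone, and the Sample size section calls for new immunostimulating therapies.

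**Working it through.** **Inputs.** n = 6 per arm, 4 arms, best arm 15 percentage points above three equal arms (all from the article). The article fixes no design base rate. I use 55.5% for illustration: it is PR + SD among evaluable patients in the earlier studies ("showing a clinical benefit (PR + SD) in 55.5% of evaluable cases"), so it is an assumption here. The range 0 to 85% is shown beside it. Arms are independent binomials.

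**Notation.** f1, F1: probability and cumulative probability of x controlled patients out of 6 in the best arm (70.5%). f0, F0: the same for each other arm (55.5%).

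**1. The article's own limit: an inferior arm leads by at least 2.**
P = 3 × Σ f0(y) × F0(y−2)² × F1(y−2)
- y = 6: 3 × 0.0292 × 0.8302² × 0.5690 = 0.0344
- y = 5: 3 × 0.1406 × 0.5484² × 0.2465 = 0.0313
- y = 4: 3 × 0.2818 × 0.2471² × 0.0666 = 0.0034
- smaller y: under 0.0001

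The sum is 6.9%. Over base rates 0–85% the maximum is 8.6%. The 10% limit in the Sample size section reproduces.

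**2. The best arm leads by at least 2.**
P = Σ f1(x) × F0(x−2)³
- x = 6: 0.1228 × 0.8302³ = 0.0703
- x = 5: 0.3083 × 0.5484³ = 0.0508
- x = 4: 0.3225 × 0.2471³ = 0.0049
- smaller x: about 0.0001

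The sum is 12.6%. No arm selected: 100 − 12.6 − 6.9 = 80.5%.

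**3. The best arm has the largest observed rate, ties split at random.**
P = Σ f1(x) × Σj C(3,j) × f0(x)^j × F0(x−1)^(3−j) / (j+1), j = 0 to 3
Outright win 34.5%, share of ties 12.3%, total 46.7% (from unrounded terms).

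**4. Range over base rates (4 arms, 15 points).**

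| Base rate | Largest rate: best arm | Gap: best arm | Gap: inferior arm | Gap: no arm |
|---|---|---|---|---|
| 0% | 71.7% | 22.4% | 0.0% | 77.6% |
| 10% | 55.0% | 17.2% | 3.6% | 79.2% |
| 30% | 47.5% | 15.7% | 8.2% | 76.2% |
| 50% | 46.4% | 13.6% | 7.8% | 78.6% |
| 55.5% | 46.7% | 12.6% | 6.9% | 80.5% |
| 70% | 49.3% | 8.0% | 2.9% | 89.0% |
| 85% | 56.3% | 1.1% | 0.0% | 98.9% |

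**5. Other readings, at 55.5%.**
- Only the three stimulated arms ranked: 55.6% (largest rate) and 19.8% (gap).
- 15% read as relative, four arms: 36.3% and 8.2%.
- All ties credited to the best arm: 62%.
- Correct given that an arm is selected: 12.6 / (12.6 + 6.9) = 65%.

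**6. What no selection tells us.** With all four arms equal at 55.5%, the gap rule selects no arm in 82.3% of trials. With one arm truly 15 points better it does so in 80.5%. The result hardly separates the two situations.

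**The case against.** Several points on the other side are sound and limit the finding.

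- **The sample size has a stated and valid basis.** A reader might infer that six per arm is left without justification. It is not: the limit on selecting an inferior arm in the Sample size section holds for a 15-point advantage. What fails is the quantity named in the trial design section.
- **The gap is worded for immune responses, and the 90% for irDCR.** Carrying the gap over to irDCR is a reasonable inference, since the same method is said to serve both endpoints with the same n and 15%, but it is not written. A reader who declines it is left with the largest observed rate, which gives 46–72%.
- **The base rate is not the design's.** The 55.5% is neither an irDCR nor a planning rate, so 13% and 47% are illustrations and the ranges carry the conclusion.
- **The 80% is not the trial's final outcome.** An undecided irDCR comparison passes to the immunological endpoint. As an illustration only, assume independent endpoints, the gap rule at both steps, an immune base rate of two-thirds and again 15 points. The second step then gives 9.4% best and 4.0% inferior. Overall: best 12.6 + 0.805 × 9.4 = 20%, inferior 6.9 + 0.805 × 4.0 = 10%, none about 70%. Selection still usually fails, but less often than at the first step.
- **It is too strong to say that no reading gives 90%.** Crediting all ties to the best arm, or conditioning on a selection, reaches 90% at extreme base rates (near 0 or above about 80%).

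The article does call the study explorative and disclaims showing which regimens are significantly better. Its caution concerns false positives, however, and does not correct a stated probability of correct selection. Nor does the article itself say that an undecided result counts against a 15-point advantage; that is a reader's likely inference from the 90%.

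**Conclusion.** The 90% is wrong as written. With 4 × 6 patients and a 15-point irDCR advantage, the best arm is selected in 46–72% of trials by largest observed rate (47% at an assumed 55.5%). Under the 2-patient gap applied to irDCR it is selected in 1–22% (13% at 55.5%), an inferior arm in at most about 9%, and no arm in about 76–99% (80% at 55.5%) at the first step. Ranking only the three stimulated arms gives 56% and 20% at 55.5%.

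These figures assume independent binomial outcomes, exactly six per arm, an absolute 15 points and equal rates in the other arms. That the 90% came from the 10% limit is an inference from the matching n and 15%; that it does not reproduce is not. The documents do not support the wider conclusions that the sample size has no valid basis or that 80% of trials end without a choice.

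**What to change.** In the trial design section, without changing the sample size:

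1. Replace the 90% sentence by the statement that, for a 15-point advantage, the 2-patient gap rule limits selection of an inferior arm to at most 10% each time it is applied.
2. Say which rule governs irDCR, the largest observed rate or the 2-patient gap, and whether the vaccine-alone arm is ranked with the others.
3. Give the probabilities of correct, inferior and no selection under that rule, with the assumed base rate and the range. Under the gap rule with four arms at 55.5% these are about 13%, 7% and 80%, with correct selection in 1–22% over base rates 0–85%.
4. Note that these are first-step figures, before the fallback to the immunological endpoint.
5. Add that selecting no arm is not evidence against a 15-point advantage.

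The cost is wording only, with no added patients. The stated performance becomes much less favourable.
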